## Discussion

A potential connection between abnormal immune response, food-derived compounds, and MDD is still poorly understood; however, increasing evidence has confirmed the importance of the interplay between microbiota, gut permeability, immune-inflammatory processes in the pathophysiology of MDD [83]. The modulation of the gut-microbiota-brain axis could therefore be a promising therapeutic target for mental illnesses [15, 16, 84]. This concept has produced a new clinical approach involving dietary interventions restoring gut eubiosis in the treatment of MDD.

A gluten-free diet and probiotic supplementation, separately and in combination, have received much attention as a potential therapeutic strategy. This approach is of particular interest as it considers that a gluten-free diet changes the microbiota profile and alters the activity of microbiota-mediated biochemical pathways [85, 86]. Notably, the microbiota is able to digest gluten. Bacterial and fungi enzymes are involved in gluten break-down and the formation of peptides with different immunogenic capacities [87, 88]. Hence, gut dysbiosis could intensify the immunogenic effect of cereal-derived compounds [89]. Studies have confirmed differences in gut microbiota of patients with celiac disease and non-celiac gluten sensitivity (NCGS) [90, 91]. Eubiosis is necessary for both appropriate gut function and restoration of intestinal barrier integrity, [87, 88, 92].

This bidirectional interaction between a GFD and microbiota suggests that the combination of a gluten-free diet and probiotic supplementation is essential for the inhibition of the immune-inflammatory cascade. However, whether the separate use of one of these interventions or their combination will be the most effective treatment strategy to regulate CNS and digestive tract functions in MDD patients has yet to be determined. Results confirming the efficacy of such a therapeutic approach would provide support for the introduction of dietary interventions as an integral part of treatment in psychiatric wards.

To the best of our knowledge, this will be the first intervention study assessing the efficacy of both probiotic supplementation and a gluten-free diet and comparing the effect of both interventions and their combination in MDD patients. The protocol and the outline were developed by a multidisciplinary researcher team. The methodology employed in the study benefited greatly from our diverse set of knowledge, experience and perspectives. Considering the highly rigoristic selection criteria, the participant group is relatively large. Rigorous procedures established for this trial will be followed by well-trained researchers to ensure that research will be conducted in accordance with standards of best practice. The measurements listed above will be introduced to reduce the potential bias related to confounding variables (e.g. smoking, physical activity, and diet).

There may be some possible limitations in the design of the study:

First, the impossibility of blinding the diet is a factor that could affect assessment of both the participant and investigator. For this reason, the researcher evaluating the severity of symptoms will not be informed as to whether the patient will be allocated to the GFD or GD arm of intervention.

Second, the lack of motivation is a symptom commonly experienced by MDD patients and could contribute to the non-attendance at the study visits, incomplete implementation of the intervention, or failure to complete the intervention.

Third, patients in the GFD groups receiving dietary advice might try to introduce other changes in food consumption (e.g. reduce the food portion size and/or consume more vegetables and fruits). Therefore, health improvement may not be specific to the implemented gluten-free diet.

Finally, recall bias in self-reporting is another potential confounder of the study. However, dietary consultation and food intake assessment during the study period should minimize the likelihood of its occurrence.

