### Study design

The trial will be a prospective, randomized, double-blind (placebo = probiotic) controlled design that will last 12 weeks. The trial was registered in the clinicaltrials.gov registry (ClinicalTrials.gov identifier: NCT03877393).

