#### Patients’ well-being

To check the effect of the intervention on the severity of depression, other psychiatric features, co-morbid symptoms, and general patient health, the following scales and questionnaires will be used:
MADRS scale (Montgomery-Asberg Depression Rating Scale) [47] for clinical assessment of depression severity will be administered by a well-trained psychiatrist. The MADRS is a 10-item scale that includes questions concerning apparent sadness, reported sadness, inner tension, reduced sleep, reduced appetite, concentration difficulties, lassitude, inability to feel, pessimistic thoughts, and suicidal thoughts. The assessment will always be performed by the same person blinded to the intervention type.BDI (Beck’s Depression Inventory [48]) for self-reporting measurement of the severity of depression. The BDI consists of 21 multiple-choice questions.SCL-90 (The Symptom Checklist-90 Questionnaire [49]) assesses the general intensity of psychopathological impairment. The SCL-90 is a self-reporting measurement tool that includes 90 items regarding the currently felt symptoms divided into nine subscales: somatization, obsessive-compulsive, interpersonal sensitivity, depression, anxiety, hostility, phobic anxiety, paranoid ideation, and psychoticism.PSS-10 (The Perceived Stress Scale [52]) includes 10 items and measures the self-reported perception of psychological stress in respondents by asking about their thoughts and feelings during the last month.CTQ Questionnaire (Childhood Trauma Questionnaire [53]) is used for the self-assessment of traumatic experiences which covers 28 items in total and consists of five subscales addressing: physical, emotional, and sexual abuse, and physical and emotional neglect.SF-36 Health Survey (The Short Form (36) Health Survey [50]) includes patients’ reports about their vitality, physical functioning, bodily pain, general health perceptions, physical role functioning, emotional role functioning, social role functioning, and mental health.The GSRS scale (The Gastrointestinal Symptoms Rating Scale [51]) is a self-administered questionnaire which assesses five symptom clusters (combined from 15 items) depicting: reflux, abdominal pain, indigestion, diarrhoea, and constipation experienced over the past week.

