### Data management and analysis plan

#### Data analysis principles

To evaluate the efficacy of the intervention on the well-being of patients, the following changes from the baseline (V1) to the end of the study (V3) will be determined as primary outcomes:
The severity of depression symptoms:
MADRS total scoreBDI total scoreThe severity of psychopathological impairment:
SCL-90 total scoreThe quality of life:
SF-36 total scoreStress levels:
PSS-10 total score

To evaluate the effect of the intervention on physiological parameters [79], the following changes will be determined as secondary outcomes:
In serum, from the screening (V0) to the end of the study (V3), levels of:
proinflammatory biomarkers: hs-CRP, Il-6, Il-1beta, and TNF-alphagluten sensitivity biomarkers: anti-TG2 IgG antibodies and anti-AGA IgG/IgA antibodiesintestinal permeability biomarkers: I-FABP/FABP-2 and LBPmetabolism biomarkers: total cholesterol, LDL cholesterol, HDL cholesterol, TG, glucose, and insulinHPA axis biomarker: cortisolliver function biomarkers: ALT and ASTIn stool, from the baseline (V1) to the end of the study (V3):
taxonomic and functional analysis of gut bacterial communitySCFAs levelsBrain activity, from the baseline (V1) to the end of the study (V3):
EEG analysisGastrointestinal symptoms, from the baseline (V1) to the end of the study (V3):
GSRS scale.

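### The remedy for the unblinded diet protects only the MADRS rater, so four self-reported primary outcomes are open-label for every comparison that crosses diet arms

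*Protocol article*

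**What the plan says.** - **Primary outcomes.** Under Data analysis principles, "the following changes from the baseline (V1) to the end of the study (V3) will be determined as primary outcomes": MADRS, BDI, SCL-90, SF-36 and PSS-10 totals. None is ranked above another, and no role is assigned by comparison.
- **Who scores them.** Under Patients' well-being, MADRS "for clinical assessment of depression severity will be administered by a well-trained psychiatrist", always by the same person, who is blinded to the intervention. BDI is "for self-reporting measurement of the severity of depression". "The SCL-90 is a self-reporting measurement tool". PSS-10 "measures the self-reported perception of psychological stress in respondents". SF-36 is described as made up of the patients' reports.
- **The diet.** The Discussion lists as its first limitation that "the impossibility of blinding the diet is a factor that could affect assessment of both the participant and investigator". The measure given in response is that "the researcher evaluating the severity of symptoms will not be informed as to whether the patient will be allocated" to the gluten-free or gluten-containing arm.
- **The label.** The Study design section describes a "prospective, randomized, double-blind (placebo = probiotic) controlled design". The title, the abstract and the Aim and hypothesis section use double-blind without that parenthesis.
- **The question asked.** The primary hypothesis under Aim and hypothesis covers the probiotic, the gluten-free diet and both together, with depressive symptoms among the targets.

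**The concern.** The stated problem has two halves, participant and investigator, and the stated remedy deals with one. Patients know whether they are avoiding gluten, and they complete four of the five primary scales. If being on the active diet leads them to expect improvement, they may report improvement, and a comparison of diet arms will show it as a diet effect.

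The diet is one of the main questions, and the Discussion says that positive results would support dietary intervention as a part of psychiatric treatment. Followed as written, the plan would let a primary diet claim rest on a self-report scale alone, with the same standing as a claim on the blinded rating.

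**Working it through.** **1. Which outcomes the remedy reaches**

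| Primary outcome | Completed by | Covered by rater blinding |
|---|---|---|
| MADRS | psychiatrist | yes |
| BDI | patient | no |
| SCL-90 | patient | no |
| SF-36 | patient | no |
| PSS-10 | patient | no |

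So 4 of 5 primary outcomes are self-reported, and the remedy reaches none of those four.

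**2. Which comparisons are exposed**

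Let expectation shift the mean self-report by *e* in both gluten-free arms and let no intervention have any true effect. The cell means are PRO-GFD = *e*, PLA-GFD = *e*, PRO-GD = 0, PLA-GD = 0.

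- Diet main effect, GFD − GD: *e*
- PRO-GFD − PLA-GD: *e* − 0 = *e*
- PRO-GFD − PRO-GD: *e* − 0 = *e*
- PRO-GFD − PLA-GFD: *e* − *e* = 0
- Probiotic main effect: (*e* + 0)/2 − (*e* + 0)/2 = 0
- Interaction: (*e* − *e*) − (0 − 0) = 0

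The bias enters whenever a contrast crosses diet arms and cancels within a diet. It cancels in the interaction only if the shift is the same with probiotic and placebo.

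**3. How large the consequence could be**

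The plan gives no figure on this point to reproduce. Its 81% power statement concerns sample size and does not bear on it.

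Inputs:
- 30 patients per arm, hence 60 per diet if arms are pooled (Randomization section).
- Two-sided 5% test: assumption.
- Expectation shift *d* of 0.1 to 0.3 SD: assumption, since the documents give none.
- True diet effect of zero: assumption.

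Formula: with *n* per side, the two-sample t statistic has 2*n* − 2 degrees of freedom and noncentrality δ = *d* × √(*n*/2). The false-positive rate is P(|T| > critical value).

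| *d* | 60 v 60: δ | rate | 30 v 30: δ | rate |
|---|---|---|---|---|
| 0 | 0 | 5% | 0 | 5% |
| 0.1 | 0.1 × √30 = 0.55 | 8.4% | 0.1 × √15 = 0.39 | 6.7% |
| 0.2 | 1.10 | 19.2% | 0.77 | 11.9% |
| 0.3 | 1.64 | 37.1% | 1.16 | 20.8% |

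The critical values are 1.980 (118 df) and 2.002 (58 df). A normal approximation gives 8.5%, 19.5% and 37.6% for 60 v 60, and 6.7%, 12.1% and 21.3% for 30 v 30. These are rates for one scale, so they contain no multiplicity component.

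**The case against.** **The limitation is disclosed and cannot be avoided.** This stands as far as it goes. The Discussion puts it first and names the participant, so nothing is concealed, and patients cannot be blinded to an eliminated food group. But disclosure does not change the list of primary outcomes, where the four exposed scales keep the same status as the protected one for every comparison. A later analysis plan could change their roles, but it could not blind the patient.

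**The trial already says what is blind.** This stands for the Study design section, which ties double-blind to placebo versus probiotic. A reader might infer that the blinding label is wrong throughout. The documents do not support that: only the title, abstract and aim lack the qualification.

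**The combination is not lost.** This stands. A reader might infer that no combination effect can be told from expectation. PRO-GFD against PLA-GFD compares blinded capsules within one diet, and the interaction is protected under additivity. Only PRO-GFD against a gluten-containing arm is exposed.

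**The pooled 60 v 60 test is not named.** This stands. The Statistical analysis section names ANOVA or Kruskal-Wallis with post-hoc tests and repeated-measures ANOVA. It does not exclude a factorial model, so both the pooled and the pairwise rates are shown.

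**Counting any of the four scales inflates the figure.** This stands. With an assumed correlation of 0.5 and 60 v 60, at least one of four scales would be significant in about 43% of trials at 0.2 SD and 67% at 0.3 SD. About 15% would occur with no expectation at all, from multiplicity alone, so those totals should not be read as expectation bias.

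**MADRS is not immune either.** This stands and shapes the fix. Its items include reported sadness, sleep, appetite and pessimistic thoughts, which draw on what the unblinded patient says. A blinded rater removes rater bias and leaves patient expectation.

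**Unequal dietary contact is uncertain.** The Elimination diet section gives the lists, guide and menus to each participant, under a heading about the gluten-free groups. The Discussion speaks of dietary advice to the gluten-free groups. The point does not depend on it: knowing the diet is enough.

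**Conclusion.** The concern holds for contrasts that cross diet arms (GFD v GD, PRO-GFD v PLA-GD, PRO-GFD v PRO-GD) and for BDI, SCL-90, SF-36 and PSS-10. On these the comparison is open-label, and the remedy that the plan offers does not reach the problem that it admits. Probiotic versus placebo within a diet is not affected.

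The count of four in five and the mismatch come straight from the text. The false-positive rates rest on an assumed shift of 0.1 to 0.3 SD, no true diet effect and a two-sided 5% test. They show what expectation could do; they do not estimate what it will do in this trial.

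This is worth correcting because it is cheap and bears on a main question. It does not invalidate the design.

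**What to change.** 1. **Data analysis principles.** For contrasts that cross diet arms, name blinded-rater MADRS as the confirmatory outcome and BDI, SCL-90, SF-36 and PSS-10 as supportive. Add that rater blinding removes rater bias but not patient expectation, so that a diet benefit on MADRS is read with that limit. For probiotic versus placebo, all five scales keep their present role.
2. **Title, abstract, and Aim and hypothesis.** Carry over the qualification from the Study design section, so that double-blind and placebo-controlled refer to the capsule. Describe the diet comparison as open-label with a blinded rater. The Study design section needs no change.

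The cost is wording and a hierarchy of outcomes: no new patients, visits or measurements. The downside is a narrower confirmatory claim for the diet on self-reported outcomes.

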## Data Availability

The datasets used and analyzed during the study will be available from the corresponding author on request.

## Abbreviations

AGA: Anti-gliadin antibodies
ALT: Alanine aminotransferase
anti TG2: antibodies against tissue transglutaminase
AST: Asparagine aminotransferase
BBB: Blood brain barrier
BDI: Beck’s Depression Inventory
BMI: Body mass index
CNS: Central nervous system
CTQ: Childhood Trauma Questionnaire
DSM-5: Diagnostic and Statistical Manual of Mental Disorders, fifth edition
EEG: Electroencephalography,
FC: Functional connectivity
FFQ: Food Frequency Questionnaire
GD: Gluten containing diet
GFD: Gluten-free diet
GI: Gastrointestinal
GSRS: Gastrointestinal Symptom Rating Scale
HbA1c: Hemoglobin glycosylated
HDL: High density lipoprotein
HPA: Hypothalamic-pituitary-adrenal
HR: Heart rate
hsCRP: high-sensitivity C reactive protein
IFABP: Intestinal fatty acid-binding protein
IgE: Immunoglobulin-E
IPAQ: International Physical Activity Questionnaire
LBP: Lipopolysaccharide binding protein
LDL: Low density lipoprotein
MADRS: Montgomery-Asberg Depression Scale
MDD: Major depressive disorder
PLA: Placebo
PPM: Parts per milllion
PRO: Probiotic
PSS-10: Perceived Stress Scale
RR: Blood pressure
SCFAs: Short chain fatty acids
SCL-90: Symptom Checklist-90 Questionnaire
SF-36: Short Form (36) Health Survey
sIgA: secretory immunoglobulin A
TG: Triglycerides
TJs: Tight junctions
TNFα: Tumor necrosis factor alpha
TSH: Thyroid stimulated hormone
V1: Baseline Visit
V1: Consultation Visit
WHO: World Health Organization
